## Abstract

**Background:**

The role of pain sensitivity in the development and maintenance of chronic pain states, impaired executive functioning, and patient recovery is being investigated. Conditioned pain modulation (CPM) is widely used to measure musculoskeletal pain associated with central sensitization (CS). Despite the recommendations of many reviews and clinical practice guidelines that exercise programs reduce pain and disability, the overall confidence in these results is considered “critically low.” The “active ingredient” of exercise programs and the dominant factor influencing CPM remain largely unknown.

The objectives of this trial are to determine:

• If different exercises cause different results on the CPM in a subgroup of people with chronic low back pain (CLBP) who are labeled as having CS pain,

• If a program of exercise interventions for 12 weeks would alter executive functioning, quality of life (QoL), disability, and pain in persons with CLBP.

• The relationship between patient characteristics, executive functions, CPM, and QoL

**Methods:**

The trial is a randomized, controlled, multi-center study with four experimental groups and one healthy control group. Both the researchers and the people in the study will be blinded to the results. This paper describes the protocol for a trial examining the effects of 12-week individualized, twice-weekly exercise sessions lasting 30 to 60 min in persons with CLBP, who are positive for CS. Participants will be randomized to receive either patient education with motor control exercises (MCE), superficial strengthening (SS), aerobic exercises (AE), or patient education alone. Another group comprised of healthy volunteers will serve as controls. The primary outcomes are changes in CPM outcomes as measured by the cold pressor test (CPT). The secondary objectives are to evaluate executive functioning, pain, disability, quality of life, and spine muscle strength. The outcomes will be measured at 3 months and at a 6-month follow-up.

**Discussion:**

The outcomes of the study will help in gaining more information and evidence about exercise-induced analgesia from the perspective of CPM. Measuring exercise outcomes will aid in scientifically prescribing exercise prescriptions in people with CLBP. The study outcomes will also assist in identifying the characteristics of individuals who will respond or respond indifferently to exercises. Investigating the relationship between the study’s various outcomes could provide information for future trials.

**Trial registration:**

Clinical Trials Registry of India (CTRI) identifier: CTRI/2022/03/041143. Registered on 16 March 2022.

**Supplementary Information:**

The online version contains supplementary material available at 10.1186/s13063-023-07316-x.

## Introduction

### Background and rationale {6a}

Chronic low back pain (CLBP) refers to low back pain (LBP) that is persistent and incapacitating for more than 3 months [1] and is unrelated to underlying illnesses such as an infection, tumor, or fracture [2]. Because the causes of most CLBP conditions are unknown, they are categorized as non-specific CLBP (NSCLBP) [3]. Studies have indicated abnormal cortical function in CLBP patients including reduced left dorsolateral prefrontal cortex activity [4]; disruption of executive functions such as multitasking ability [5], sustained attention and working memory [6, 7]; longer processing time [8]; and substantial disturbances in mental flexibility, delayed memory, and psychomotor speed [9].

The role of pain sensitivity in the development and maintenance of chronic pain states and its influence on patient recovery are unclear and thus being investigated. Impaired functioning of descending anti-nociceptive mechanisms and activation of the descending and ascending pain facilitatory pathways facilitate overall pain transmission. Central sensitization (CS) is the increased responsiveness of nociceptive neurons in the central nervous system (CNS) to their normal or subthreshold afferent input [10]. Conditioned pain modulation (CPM) is extensively used to measure CS-associated musculoskeletal pain and refers to the quantitative sensory test used to assess the functionality of endogenous pain inhibition in the CNS [11]. CPM is directly related to the cognitive performance and self-reported health-related quality of life (QoL) [12].

Although persons with chronic pain are believed to have lower CPM inhibition, Sluka (2016) reported that some individuals with fibromyalgia and healthy persons exhibit normal and abnormal responses to CPM, respectively [13]. Evidence for CPM alterations in CLBP patients is mixed, with studies revealing impaired [14], normal [15], and facilitated [16] CPM compared with healthy controls. Mlekusch et al. (2016) evaluated endogenous pain modulation by using the cold pressor test (CPT) in persons with and without LBP and reported that the CPM effect declined more rapidly in the LBP group than in the normal population [17].

Exercises reduce the overall sensitivity of the CNS [18] by activating exercise-induced endogenous analgesia and spinal inhibitory mechanisms. Some studies have concluded that a bout of aerobic exercise (AE) could reduce sensitivity to painful stimuli in healthy individuals; however, other studies have reported contradictory results, with AE producing both hyper and hypoalgesic responses [19]. A study revealed an increase and a decrease in mean pain thresholds, respectively, in patients with CLBP and chronic fatigue syndrome as a response to exercise (submaximal AE program on a bicycle ergometer) [20]. Vaegter et al. (2016) examined CPM and exercise-induced hypoalgesia (EIH) in patients with chronic musculoskeletal pain under two different training conditions (bicycling and isometric contraction): one with high pain sensitivity and the other with low pain sensitivity. A partial impairment of CPM and EIH was observed in patients with high pain sensitivity compared with that in patients with low pain sensitivity [21]. Past reviews and guidelines have barely provided sufficient details about the indications of different exercise types to be used in clinical practice.

Few studies have investigated how different exercise doses affect EIH in chronic pain patients. Other studies have compared the EIH response following an AE condition with a predefined intensity (such as 75% of the maximal heart rate) to that with a self-selected intensity [22, 23]. Furthermore, numerous studies on EIH in chronic pain populations have relied on exercise doses that might not accurately reflect clinical practice, such as AE protocols lasting for < 15 min [22–24] and isometric exercises at low loads (10–30% of the maximum voluntary contraction) instead of dynamic resistance exercises [25, 26].

No previous study has investigated the associations between CPM outcomes, executive functions, and QoL in CLBP patients from the perspective of exercise interventions. Additional studies investigating the effects of varied exercise types and dosage on EIH in chronic pain populations that more closely resemble those observed in clinical practice are warranted. Furthermore, knowledge about the ideal frequency and types of exercise to be recommended in an exercise prescription is limited. We postulated that studying the effect of three types of exercise interventions in a subgroup of CS-positive patients and exploring the relationship between CPM responses, CLBP-related outcomes, and executive functions would increase our understanding regarding exercise prescriptions. This is crucial because pain sensitization-targeting interventions are limited and evidence for the effectiveness of exercise interventions is inconclusive.

### Objectives {7}

The primary objective of the present study is to determine if different exercise types produce varied outputs on CPM in a subgroup of CLBP patients classified as having CS pain. The secondary objectives are to evaluate if a 12-week exercise intervention program would alter executive functioning, QoL, disability, and pain and to examine the relationship between patient characteristics, executive functions, CPM, and QoL in CLBP patients.

### Trial design {8}

This is a randomized, controlled, double-blinded study determining how CPM changes in response to three types of active exercises in CS-positive CLBP patients. Participants will be randomized to undergo 12 weeks of the motor control exercise (MCE), superficial strengthening (SS), or AE combined with patient education or patient education alone. This active treatment concurrent control design will be used to demonstrate superiority of one exercise group over another. All patients will be allocated in a 1:1:1:1 ratio using random number tables. All participants will receive advice to stay active. Another no-pain control group will also be recruited. The intervention will be provided for 12 weeks. An independent assessor will collect data at baseline (t0), after intervention at 3 months (t1), and at the 6-month follow-up (t2). Outcome measures include CPT for measuring CPM, letter–number sequencing subtest in the Wechsler Adult Intelligence Scale-III Edition (WAIS-III), Stroop neurophysiological test, QoL assessed using the abbreviated WHOQOL-BREF questionnaire, isometric muscle strength of spine and hip muscles, the Oswestry Disability Index (ODI) questionnaire, and the Numerical Pain Rating Scale (NPRS). Table 1 and Fig. 1 present the study design and flowchart, respectively. The research ethics approval was granted by the Integral University, India (IIAHSR/DO/PT/2022/23), and Composite Regional Centre for Skill Development, Rehabilitation, and Empowerment of Persons with Disabilities, India (CRCL/Ph.D. Data Collection/2021–22/1556). The study is designed according to the Consolidated Standards of Reporting Trials (CONSORT) guidelines and reported according to the Standard Protocol Items: Recommendations for Interventional Trials (SPIRIT) checklist. The study will use a 5 (between subjects − type of exercise interventions: MCE vs. AE vs. SS vs. patient education vs. no-pain control) × 3 (within subjects − time: before vs. after vs. 3 months after the intervention) mixed design.

**Table 1 Tab1:**
[figure not shown]
Schedule of enrolment, intervention and assessment

*CPM* Conditioned pain modulation, *NPRS* Numerical Pain Rating Scale, *ODI* Oswestry Disability Index, *QoL* Quality of life

**Fig. 1 Fig1:**
[figure not shown]
Schematic of study design

## Methods: participants, interventions, and outcomes

### Study setting {9}

The study will be conducted between August 2022 and October 2023. In total, 172 participants (both male and female) aged between 18 and 59 years who have CLBP and are positive for CS-related signs and symptoms will be recruited from the Outpatient Physiotherapy Departments of the Integral University and the Composite Regional Centre for Skill Development, Rehabilitation, and Empowerment of Persons with Disabilities. Similarly, we will recruit a no-pain control population (*n* = 43).

### Eligibility criteria {10}

The inclusion criteria for the participants are as follows: age between 18 and 59 years, male or female sex, diagnosed with NSCLBP satisfying the definition provided in the European guidelines for NSCLBP management [27], and being positive for CS-related signs and symptoms [28]. Further, using the Physical Activity Readiness Questionnaire, all participants will be screened for contraindications to exercise [29]. Table 2 presents the complete inclusion and exclusion criteria.

**Table 2 Tab2:** Inclusion and exclusion criteria

Inclusion criteria	Exclusion criteria
• Persons between 18 and 59 years of age • CLBP of more than 3 months duration • Pain intensity of more than 4 on the NPRS • Clear mechanical basis of the symptoms • Positive for CS-related sign and symptoms • Cognitively intact [Mini-Mental State Examination score > 24] • Basic working knowledge of English language	• Attributable to a recognizable, known specific pathology (e.g., infection, tumor, osteoporosis, fracture, structural deformity, inflammatory disorder (e.g., ankylosing spondylitis) or cauda equina syndrome) • Participants who are contra-indicated to participate in physical activity • Participants who have undertaken any surgical procedures to spine or suffering from symptomatic spine diseases • Participants, who report acute pain within 48 h prior to the appointment • No corticosteroids or other drug therapy in the preceding 2 weeks • Participants suffering from any other chronic pain condition, high blood pressure, Raynaud’s disease, frostbite, any open cut, sore, or bone fracture, other major illness such as cancer, visual and/or hearing impairment, and psychiatric disorders • Presence of clinical signs or symptoms of radiculopathy

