### Primary outcome measure

#### CPM

The CPT will be used to measure CPM. For the conditioning stimulus, the participants’ non-dominant hand will be immersed in a bucket with temperature-controlled cold water (1 °C–4 °C), monitored by a thermometer for up to 1 min. The participant has to remain with the hand immersed in water without making muscle contractions or changes in position. Withdrawal from the water will be allowed if the patient can no longer tolerate the painful stimulus. This test will be conducted in a room with controlled room temperature, humidity, lighting, and noise.

Using a digital pressure algometer, the pressure pain threshold (PPT) will be performed in the forearm regions and tibialis anterior muscle of the dominant limbs before and after 1 min of the CPT. The tibialis anterior muscle and the distal part of the dorsal forearm, which had not been immersed in water, will be evaluated because of the lack of their relationship with the participants’ musculoskeletal complaints.

The operation of the pressure algometer and PPT measurement will be explained to the patients, and a practice test will be conducted on the patients’ dominant forearm to ensure that the test has been understood. Force will gradually be increased [1 kg-force/s] until the feeling of pressure changes to pain. The PPT will be recorded in kilograms force [Kgf]. The PPT will be repeated three times and the mean will be calculated to give the baseline PPT. The efficiency of the descending nociceptive inhibitory system will be evaluated by calculating the difference between PPT values in CPT (final cost − initial value) [41].

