### Study strengths

The study intends to investigate only those outcome measures that have good psychometric properties, have been used extensively in research, and can be measured quickly. We will only recruit participants aged between 18 and 59 years as a previous study has hinted at a decline in endogenous pain modulatory and CPM functions with advancing age [66]. Studying the association between executive functioning, CPM, and exercises will be a major addition to the results as a previous study has indicated that this relationship is selectively sensitive and the positive effect observed on animals do not translate in humans [67]. Further, we will apply the optimal exercise dose in each group based on the methodology used in previous works.

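### Which Table 2 criteria bind the 43 no-pain controls is undefined, and these non-randomised controls enter the ANOVA contrasts with no age or sex matching or adjustment

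*Protocol article*

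**What the plan says.** Under Eligibility criteria {10}, the Protocol article names a few main criteria and then says "Table 2 presents the complete inclusion and exclusion criteria". The inclusion column of Table 2 contains "CLBP of more than 3 months duration", "Pain intensity of more than 4 on the NPRS", a mechanical basis for the symptoms, and "Positive for CS-related sign and symptoms". It also has lines on age, cognition and English that anyone could meet. The exclusion column mixes back-specific items (specific spinal pathology, spinal surgery, radiculopathy) with general ones (high blood pressure, Raynaud's disease, frostbite, open cuts, major illness).

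Study setting {9} describes "172 participants (both male and female) aged between 18 and 59 years who have CLBP" and signs of central sensitization, and then adds "Similarly, we will recruit a no-pain control population", with n = 43. Intervention description {11a} calls this group healthy volunteers. Neither place defines no-pain or gives the group entry criteria of its own.

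Trial design {8} and Statistical methods {20a,b} make this group the fifth level of the between-subject factor in a 5 × 3 mixed ANOVA, followed by Tukey comparisons. The 1:1:1:1 allocation covers patients only. The outcome is the cold pressor test, in which the participant's "hand will be immersed in a bucket with temperature-controlled cold water".

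Study strengths explains the age limit by saying that "a previous study has hinted at a decline in endogenous pain modulatory and CPM functions with advancing age". Study limitations says that gender, body mass index and physical activity will not be considered as confounders.

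**The concern.** There are two linked problems.

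First, a list described as complete shuts out one of the five groups to be analysed. A recruiter has to decide which lines to ignore for a volunteer. Two sites could decide differently, and both could claim to follow the protocol. The uncertainty extends to the exclusions that bear on cold immersion.

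Second, the controls are a non-randomised group chosen by rules that are not written down, and they are compared with patients without matching or adjustment. Explanation for the choice of comparators {6b} expects the control populations, the no-pain group among them, to help show whether the interventions work. If controls and patients differ in age or sex, and conditioned pain modulation varies with either, the patient-control contrast mixes the effect of having pain with the effect of group make-up.

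**Working it through.** **1. Table 2 against a no-pain volunteer**

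| Table 2 item | Can a no-pain volunteer meet it, or be covered by it? |
|---|---|
| Chronic low back pain over 3 months | No |
| NPRS above 4 | No |
| Mechanical basis of symptoms | No |
| Positive for central sensitization signs | No |
| Age 18 to 59, cognition, English | Yes; the age line is worded for persons generally |
| Exclusions: high blood pressure, Raynaud's disease, frostbite, open cuts and similar | Yes; worded for participants, with no group named |

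Four inclusion lines are impossible for controls. The rest could apply, but the text does not separate the two kinds. The word *participants* does not settle it. Intervention description {11a} uses it for the 172 patients alone, while the cold pressor description uses it for everyone immersed.

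**2. Handling of composition**

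- Matching on age or sex: none stated.
- Covariates in the repeated-measures ANOVA or the Tukey contrasts: none stated.
- Multiple linear regression: planned to find characteristics of responders, not to adjust patient-control contrasts.
- Table 4: age and gender are collected in both patients and controls, so adjustment is possible with data already planned.
- Age limit: even if it binds the controls, it spans 59 − 18 = 41 years, so the groups could still differ in age.

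**3. The plan's own figures**

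Sample size {14} gives SD 100 kPa, difference 80 kPa, two-sided alpha 0.05, 30 per group, 87% power and 30% dropout.

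- Standardised difference: 80/100 = 0.8.
- Power with 30 per group: 87.3% by the normal approximation, and 86.1% by the noncentral t with 58 df and noncentrality 0.8 × √(30/2) = 3.10. The stated 87% is reproduced.
- Recruitment: 30/(1 − 0.30) = 42.9, rounded up to 43. 4 × 43 = 172 patients; with 43 controls, 215.

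These figures are sound and are not the issue.

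**4. Illustration of what composition can do**

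The documents give no age or sex effect on conditioned pain modulation, so the shift is an assumption shown over a range. Let *d* be a patient-control difference due only to composition, in SD units. For a two-sample t-test at two-sided 0.05 with *n* per group, df = 2n − 2 and noncentrality = d × √(n/2). The probability of a significant result is:

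| Assumed shift | At SD 100 kPa | 43 vs 43 | 30 vs 30 |
|---|---|---|---|
| 0.2 SD | 20 kPa | 15% | 12% |
| 0.3 SD | 30 kPa | 28% | 21% |
| 0.4 SD | 40 kPa | 45% | 33% |
| 0.5 SD | 50 kPa | 63% | 48% |

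With no shift the rate is 5%. The table is for one unadjusted pairwise comparison at a single time point. Tukey's wider critical value would lower these rates. The SD of 100 kPa was stated for the exercise groups, so using it for controls is a further assumption. A shift that stays constant over time appears in the group means but cancels in the group-by-time interaction.

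**The case against.** A reader might infer that the volunteers undergo cold immersion with no exclusions at all. The documents do not support that. The general exclusions are worded for participants, the Physical Activity Readiness Questionnaire is applied to all participants, and the cold pressor section uses the same word for those immersed. It would be inconsistent to count controls as participants for the exposure but not for the exclusions. The natural reading is that the pain-specific lines define patients and the rest covers everyone. A reader might also infer that controls have a different age range. That is not shown either: Study strengths limits participants in general to ages 18 to 59, and Study setting introduces the controls with *Similarly*, directly after giving the patients' age range.

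The word *complete* can also be taken to mean only that Table 2 fills out the short patient list just before it. Control criteria might then stand in a fuller document, and the schedule and study schematic are not visible here.

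On comparability, age, gender and body mass index are collected for controls and baseline characteristics are compared between groups, so imbalance would be seen. The article also openly lists some unaddressed confounders. The primary objective concerns exercise types among randomised patients.

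Much of this stands, and it limits the point on eligibility to a lack of definition. It does not answer the point on comparability. Seeing an imbalance at baseline does not remove it from the contrasts, and admitting confounders as a limitation does not justify leaving out an adjustment that the collected data allow.

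**Conclusion.** The concern holds in a limited form. Table 2 cannot be applied to the no-pain group as written, and which of its lines bind the 43 controls is undefined. The control group is not randomised, yet it enters the ANOVA and Tukey contrasts with no age or sex matching or adjustment, although the article itself names age as a likely influence on the primary outcome.

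The size of any bias cannot be derived from the documents. The 15% to 63% range at 43 versus 43 shows what an assumed shift of 0.2 to 0.5 SD would do in a simple comparison; it is not an estimate for this trial.

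The comparison among the four randomised arms, and so the primary objective, is unaffected. This is a cheap improvement to a secondary contrast and a needed clarification of eligibility, not a flaw in the core of the trial.

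**What to change.** Add a no-pain column to Table 2. In it, replace the four pain-specific inclusion lines with an explicit definition of no-pain, keep the age, cognition and language lines, and state that the exclusions not specific to back pain apply to controls as well.

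Then do one of the following:

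- recruit controls by frequency matching to the patients' age-band and sex distribution; or
- adjust the patient-control contrasts for age and sex, both already collected under Table 4.

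In either case, say that patient-control contrasts are non-randomised comparisons, separate from those among the four randomised arms.

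The cost is a wording change, plus slightly slower control recruitment if matching is chosen or a little more analysis if adjustment is chosen. If recruitment of controls is already under way, adjustment remains available without changing who is enrolled. The randomised arms and the sample size do not change.
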